#### **2.2.2 Self-designed questionnaires to determine the satisfaction with training, method of implementation and the impact of training on the knowledge of health care professionals**

Self-designed questionnaires will be developed to monitor the attitudes of the health care professionals towards interprofessional practice (Appendix ii). The questionnaire to monitor the knowledge of health professionals on interprofessional practice and ICF (Appendix iii) and questionnaire to determine the satisfaction of health care professionals with ICF training and the method of implementation (Appendix iv).

### **2.2.3 Auditing the quality of patient's records, referral and discharge note**

A checklist will be developed and validated to determine the degree to which all aspects of the patients' health status and functioning are included in patients' records, and how referral and discharge is made. Auditing patient record checklist (Appendix v) to be used with ICF checklist (vi).

### **2.2.4 Validity and Reliability of the instruments**

If a study will need to develop a new questionnaire, this must be piloted and validated in order to check whether it is measuring what it is supposed to measure (validity) and is it doing it consistently (reliability) (Chiaburu & Lindsay, 2008). This will be considered in this study, as it will involve developing new instruments in order to monitor appropriateness of the content, wording of questions, type and form, level of sophistication of language, sequence and how is data sought from the respondents. After development of the questionnaires, validity and reliability will be assured. A sample of 50 health care professionals and 100 patients' records will be sufficient to ensure validity and reliability of the instruments. According to the Institute of Health and Care Research (2010), a sample size of at least 50-100 participants is required to ensure the validity and reliability. The folders will be assessed until the raters of folders can do it reliably. Example: If there is 80% agreement after 20 folders, there is no need to continue. If not, the number will be increased.

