### **3.1.5 Data analysis**

Data analysis will be performed using STATISTICA. Descriptive statistics will be used to describe the characteristics of health professionals, such as frequency and percentage, mean and standard deviation. Within-group analysis will be used. The dependent t-Test will be used to compare the means before and after intervention (training) to detect whether there are any statistically significant differences between two means. Data will be presented in forms of tables, Scatterplots, and graphs. The ICC for absolute agreement between the two raters' scores of the audit of patient records will be used to determine the reliability of the scoring. The accuracy of interpretation of folders will be indicated by a set of ten folders of patients discharged longer than 6 months ago, assessed by researcher and research assistant (s), Data entered and compared, discussion and consensus reached. A further 10 files assessed and this process will continue until 80% agreement is reached.

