#### ***3.2.2.2 Sample size calculation***

It is anticipated that a 20% (8) sample of 40 district hospitals will allow the outcomes to be generalised to the other hospitals. In their study, Zegers et al. (2007) reviewing patients records in Dutch hospital, a random sample of 20% of the hospitals was selected and the results were

generalized. At each hospital all the relevant health professionals will be included in the training so the sample will be one of convenience. The primary outcome of this study will be the improved interprofessional practice within the district hospitals and comprehensiveness of the patients' records demonstrated by the scores. A sample size calculation will be done once the needed tools have been finalised and the mean and standard deviation calculated during a feasibility study. However as multi-level regression analysis will be done to account for the effect of clustering, a sample of 800 patients records (100 from each hospital) should allow for the analysis of at least 80 variables. This is a large number but, as it is anticipated that the effect size will be small due to the presence of so many confounding variables, a large sample size will be required to prevent a Type II error from occurring.

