**Thank you very much for taking part in this research**

## 5.5 Appendix v: Checklist for auditing patients' records to be used with ICF checklist

One form will be completed for each patient record. Please place a sign ☒ in the box to indicate a positive response (only **one (1)** answer per statement).

| A. Informed consent                                                                                                            | Yes                      | No                       | N/A                      |
|--------------------------------------------------------------------------------------------------------------------------------|--------------------------|--------------------------|--------------------------|
| 1. The patient's consent is documented                                                                                         |  |  |  |
| 2. The patient's consent is signed                                                                                             |  |  |  |
| B. Patient's demographic information                                                                                    |                          |                          |                          |
| 3. Medical record number                                                                                                       |  |  |  |
| 4. Patient's name                                                                                                              |  |  |  |
| 5. Patient's gender                                                                                                            |  |  |  |
| 6. Date of birth/ Age                                                                                                          |  |  |  |
| 7. Address                                                                                                                     |  |  |  |

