## 5.6 Appendix vi: International Classification of Functioning Disability and Health (ICF) checklist

One form will be completed for each patient record. Please place a sign ☒ in the box to indicate a positive response (only **one (1)** answer per statement).

| Activity Limitation & Participation Restriction                         |                          |                          |
|-------------------------------------------------------------------------|--------------------------|--------------------------|
| d1. LEARNING AND APPLYING KNOWLEDGE                                     | Yes                      | No                       |
| d110 Watching                                                           |  |  |
| d115 Listening                                                          |  |  |
| d140 Learning to read                                                   |  |  |
| d145 Learning to write                                                  |  |  |
| d150 Learning to calculate ( arithmetic )                        |  |  |
| d175 Solving problems                                                   |  |  |
| d2. GENERAL TASKS AND DEMANDS                                           |                          |                          |
| d210 Undertaking a single task                                          |  |  |
| d220 Undertaking multiple tasks                                         |  |  |
| d3. COMMUNICATION                                                       |                          |                          |
| d310 Communicating with -- receiving -- spoken messages                 |  |  |
| d315 Communicating with -- receiving -- non-verbal messages             |  |  |
| d330 Speaking                                                           |  |  |
| d335 Producing non-verbal messages                                      |  |  |

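### Rater calibration stops at raw 80% agreement, which raters at chance on the content items could reach under some item prevalences; the planned ICC would expose them but has no minimum and does not control stopping

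*Combined protocol and SAP*

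**What the plan says.** Section 2.2.4 says folders will be assessed until the raters can score them reliably, and gives as an example: "If there is 80% agreement after 20 folders, there is no need to continue". The next sentence is "If not, the number will be increased".

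Section 3.1.5 turns this into a procedure. The researcher and the research assistant(s) score ten folders, compare, discuss and reach consensus, and then: "A further 10 files assessed and this process will continue until 80% agreement is reached".

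The same section also plans a second measure: "The ICC for absolute agreement between the two raters' scores of the audit of patient records will be used to determine" the reliability of scoring. No minimum value, interval or number of folders is attached to it, and nothing in the plan depends on its result.

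The audit form is Appendix v ("One form will be completed for each patient record"). It has 30 items answered Yes, No or N/A. Items 17 and 18 instead take a count from the ICF checklist in Appendix vi. Scores for the completeness of records are part of the primary outcome (section 3.2.2.2: "The primary outcome of this study will be the improved interprofessional practice within the district hospitals and comprehensiveness of the patients' records").

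**The concern.** Raw percentage agreement is easy to reach when many items have an obvious answer or are nearly always answered the same way. Items 1 to 13 of Appendix v are consent and demographic fields, such as name or admission date, that two raters will rarely dispute. Items 14 to 30 carry the ICF and interprofessional question. Section 1.2 says that assessment and management in Rwanda is directed at the condition or impairment, and section 3.1.5 calibrates on folders of patients discharged more than six months earlier. Functioning and environmental items may therefore be rare in the calibration folders, although the documents do not say how rare.

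If so, two raters could reach 80% without agreeing on the content items beyond chance. Repeating sets until one passes gives further opportunities. Unreliable content scoring would add noise to one part of the primary outcome, and section 4.1 plans double data entry but no repeat audit.

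**Working it through.** **No derivation to reproduce.** The 80% is a chosen threshold. The check asks what it demands of the content items.

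**Inputs from the documents**
- 30 items in Appendix v: 13 consent or demographic (1-13) and 17 content (14-30).
- Threshold 80%; 20 folders (section 2.2.4) or sets of ten (section 3.1.5).

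**Assumptions, none stated in the documents**
- Agreement is pooled over items.
- The 13 clerical items are always agreed.
- Content items have two categories and a common 'yes' rate p.
- The raters tick content items independently of each other (kappa 0), and items are independent.

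**Step 1. What 80% requires of the content items.** 0.80 × 30 = 24 items agreed. (24 − 13)/17 = 11/17 = 0.647, or about 65%.

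**Step 2. Agreement by chance.** Per content item, Pe = p² + (1 − p)². Over the form, (13 + 17·Pe)/30. At p = 0.20: Pe = 0.04 + 0.64 = 0.68, and (13 + 11.56)/30 = 81.9%. The formula is symmetric, so an 80% 'yes' rate gives the same result.

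**Step 3. Probability of passing.** On 20 folders there are 600 comparisons and 480 must agree. The clerical items supply 260, so 220 of 340 content comparisons are needed: P(Bin(340, Pe) ≥ 220). For one set of ten: P(Bin(170, Pe) ≥ 110). For five sets: 1 − (1 − P)⁵, which assumes no learning between sets.

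| 'Yes' rate p | Pe | Expected overall agreement | Pass on 20 folders | Pass within five sets of ten |
|---|---|---|---|---|
| 15% | 0.745 | 85.6% | about 100% | about 100% |
| 20% | 0.680 | 81.9% | 91% | above 99.9% |
| 25% | 0.625 | 78.8% | 22% | 1 − (1 − 0.305)⁵ = 84% |
| 30% | 0.580 | 76.2% | 0.7% | 1 − (1 − 0.044)⁵ = 20% |
| 50% | 0.500 | 71.7% | essentially 0 | under 0.1% |

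**Step 4. Sensitivity to the other assumptions** (p = 20%, 20 folders, base case 91%)
- 5% N/A: Pe = 0.20² + 0.75² + 0.05² = 0.605; overall 77.6%; pass 6%.
- 10% N/A: Pe = 0.20² + 0.70² + 0.10² = 0.54; overall 73.9%; pass 0.004%.
- Counts in items 17-18 never match: (13 + 15 × 0.68)/30 = 77.3%; pass 2.6%. If they match 30% of the time: pass 34%.
- Clerical agreement 95% instead of 100%: (12.35 + 11.56)/30 = 79.7%; pass 45%. At p = 15% it stays at 99%.

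**Step 5. A different unit.** If each content item separately had to reach 16 of 20, the chance pass at p = 20% would be 18% for one item and about 3 × 10⁻¹³ for all 17.

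**The case against.** The strongest case against has four parts.

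1. **The plan does not rest on 80% alone.** Section 3.1.5 names the absolute-agreement ICC as the measure of scoring reliability. Raters at chance on the content items would be expected to show an ICC near zero on a content score, and this would be visible in the feasibility phase, where section 3.1.4 allows the outcome measures to be amended. This stands. A reader might infer that the plan cannot show the audit score to be reliable; that is too strong. What remains is that a poor ICC has no stated consequence, while 80% agreement does.

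2. **The pass probabilities are fragile.** They need 'yes' rates that the documents do not give, pooled agreement, two-category items and near-perfect clerical agreement. The real form has N/A boxes and two counts. This also stands. The 91% is one point in a range that runs from about 100% to practically zero.

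3. **The figure in section 2.2.4 is an example, and discussion between sets should produce real learning.** Both are true, so the five-set figures are upper values for luck alone. But section 3.1.5 states the same 80% as the operating procedure, without a limit on repeats.

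4. **The trial auditor is not tied to the rule.** A reader might multiply 100 records × 8 hospitals × 4 occasions = 3,200 audits and say that an unreliable auditor could be cleared for all of them by the 80% rule. Section 4 says only that the auditor will be trained and cites no agreement criterion, so the documents do not support that link. They do leave the auditor with no stated criterion.

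**Conclusion.** The point holds as a weakness in the stopping rule. Calibration ends on raw agreement with no chance correction, unit or limit on repeats, and the better measure already in the plan neither has a minimum nor controls the decision. On pooled items with the clerical fields agreed, 65% agreement on the content items is enough. Whether raters at chance on those items would actually pass depends on the 'yes' rate: very likely at 20% or below, possible at 25%, unlikely on 20 folders at 30%, and much less likely if N/A answers or count mismatches are common. The documents do not settle which applies. They do not support saying that chance-level raters will pass, or that the trial's audits will be unreliable. No effect on trial power or on the treatment estimate has been quantified.

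**What to change.** In sections 2.2.4 and 3.1.5:
- Keep the sets of ten folders with discussion, as training only. They do not count towards clearance.
- Then have the two raters independently score a fresh set of fixed size, without discussion, from the 100 feasibility records already planned.
- Make clearance depend on a minimum, set in advance, for the planned absolute-agreement ICC on a defined content score (items 14-30, stating how the counts in items 17-18 and N/A answers enter). A value of 0.75 would serve as an example; it is a proposal, not a figure from the documents. Report the ICC with its 95% interval.
- Report agreement and kappa item by item, as description. Do not compute one kappa on stacked items: differences in prevalence between items can make it high even when raters agree no better than chance within each item.

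In section 4, state that the trial auditor must meet the same criterion before auditing trial records.

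The cost is some additional double-rated folders beyond the 20 in the example, and possibly another training round. No new records or new type of measure are needed for the clearance decision.

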#### ***2.2.4.1 Content validity and Construct validity***

To ensure the content validity, the researcher will present the content of questionnaire in a panel of minimum 3 experts to review for the relevance and clarity of the items in relation to what the questionnaires are intended to measure, and also to check the flow of ideas. Content and construct validity will also be checked through cognitive debriefing by inviting a team of health care professionals to discuss on the clarity and understanding of the questions.

#### ***2.2.4.2 Reliability***

To ensure the reliability of the instruments, internal consistency will be established through the use of Cronbach's Alpha as coefficient of the internal consistency for reliability test. The Cronbach's Alpha coefficient will be set at  $>0.70$  to indicate internal consistency.

### 3 Methodology - Feasibility study

Prior to the main study, a feasibility study will be carried out in one selected district hospital. This is Nyamata hospital which has been selected purposively. Nyamata Hospital has the capacity of 164 beds, 14 medical doctors, 3 social workers, 79 nurses, 3 physiotherapists, and 2 nutritionists(Nyamata Hosiptal, 2012). A feasibility study is usually used to determine if the intended intervention is appropriate for further study (Taylor, Russ-Eft & Chan, 2005). This study will enable the researcher to answer the question “Can this study be done?” This study will also enable the researcher to estimate some important parameters that will be needed in the design of the main study. These could include the time needed to collect and analyse data, willingness to participate, availability and suitability of data, feasibility and duration of training, and designing a suitable outcome measure. The feasibility study will also determine if patients’ records reflect the actual practice in the hospitals.

[figure not shown]

**Figure 2: Feasibility study framework**

#### 3.1.1 Study design

In the feasibility study, a pre-experimental design using one group pre-test/post-test study will be used. A single selected group will be observed at two time points, once before the intervention and

once after the intervention (L.Heffner, 2004). The knowledge and attitudes of health care professionals regarding interprofessional practice will be assessed before and after a training session. The audit of medical records will also be performed. As there is no control group or randomisation to an intervention group, it is not possible to assign any change in the outcome exclusively to the intervention. However, it will give useful information with regards to planning the main experimental study.

### **3.1.2 Population and sampling**

The population for the study will include Medical doctors (General Practitioners), Physiotherapists, Mental Health/Clinical psychologist, Nurses, Social Worker, nutritionist/dietetic working in one selected District hospital (Nyamata hospital). Patients' records for discharged patients will also be included in the study. A purposive sampling method will be used in selecting the hospital, in that the hospital authorities must be ready and willing to participate in this feasibility study. A sample of convenience will be used with regard to health professionals and patients' records under the study.

As generalisability of the results is not required, the study will use a sample of convenience and recruit all eligible staff members who wish to take part in the study; and records of 100 patients on discharge will be recruited to test the feasibility, validity and reliability of the outcome measures.

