#### **Medical records**

A stratified sampling method will also be used to select the patients' medical records that will meet the inclusion criteria to be involved in the study. It is anticipated to have a maximum of 100 patients' records per hospital. In each hospital, 100 patients' records will be audited at each occasion: baseline, two months, four months, and six months after intervention. Only the records of

discharged patients will be audited as well the records of discharged patients during two months of data collection.

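### The 100 feasibility folders are a convenience sample, yet their mean and SD are to feed the trial's sample size, and such a set cannot give a data-availability rate

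*Combined protocol and SAP*

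**What the plan says.** **How the feasibility folders are chosen.** Section 3.1.2 gives the reason "As generalisability of the results is not required, the study will use a sample of convenience" and then states that "records of 100 patients on discharge will be recruited to test the feasibility, validity and reliability of the outcome measures". It names no sampling frame, order of selection or rule for folders that cannot be found or used. Section 3.1.4 adds that discharge data come from the orthopaedic/surgical, medical and paediatric wards. The plan does not say how the 100 divide between folders from before and after the training.

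**What the results are for.** Section 3 says the feasibility study will "estimate some important parameters that will be needed in the design of the main study", and that these could include "willingness to participate, availability and suitability of data". Section 3.2.2.2 says the trial's sample size calculation will follow once the tools are final and "the mean and standard deviation calculated during a feasibility study".

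**How the trial chooses folders.** Section 3.2.2.1 requires a discharged patient with a stay of at least five days on one of the three wards. Section 3.2.2.3 says "A stratified sampling method will also be used to select" the records, without naming strata or a random draw. Section 4 describes auditing every discharged patient's record up to a ceiling of 100 per hospital.

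**Access.** Under sections 3.1.4, 4.2 and 4.2.1, baseline folders are released by the hospital superintendent, while post-training folders need permission from the patient or from a parent or guardian.

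**The concern.** The reason given for convenience sampling is that nothing has to carry over, but two uses of the folder results require exactly that.

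First, the audit mean and SD are planning inputs for the trial. For a fixed raw difference the required number of records is proportional to the SD squared, so a selected set of folders can distort the planned size. Section 3.2.2.2 expects a small effect and wants to avoid a Type II error, so an SD that is too low would defeat its purpose.

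Second, availability is a proportion: usable folders over folders sought. If 100 folders are gathered by taking those to hand, the numerator is fixed at 100 and the denominator is never recorded.

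Both problems would remain in a calculation confined to the feasibility hospital. They are separate from the question of using only one hospital.

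**Working it through.** **1. The plan's own figures.** From section 3.2.2.2: 0.20 × 40 = 8 hospitals; 8 × 100 = 800 records; 800 / 80 = 10 records per variable. These reproduce exactly. None of them uses a feasibility estimate, so any selection error would enter at the calculation still to come.

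**2. Feasibility and trial folders side by side.**

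| Item | Feasibility | Trial |
|---|---|---|
| Wards | three wards (3.1.4) | same three (3.2.2.1) |
| Discharged | yes (3.1.2) | yes (3.2.2.1) |
| Stay of at least five days | not stated | required (3.2.2.1) |
| Draw | convenience (3.1.2) | stratified (3.2.2.3), or all discharges up to 100 (4) |
| Missing or unusable folders | no rule | no rule |

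Wards and discharge status already match. The length-of-stay criterion is not stated for feasibility folders. The draw differs in name, although the plan's two accounts of the trial draw leave the contrast unsettled.

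**3. What selection could do to the mean and SD.** The plan gives no mean or SD, so this is an illustration. Assume a normal audit score with true SD 1, and that selection misses the thinnest fraction q. With a = z_q (the q quantile), λ = φ(a)/(1 − q), mean shift = λ and variance = 1 + aλ − λ²:

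| q | a | λ (mean too high by, in SDs) | Variance | SD | SD understated by |
|---|---|---|---|---|---|
| 0.10 | −1.28 | 0.19 | 0.712 | 0.844 | 16% |
| 0.25 | −0.67 | 0.42 | 0.535 | 0.731 | 27% |
| 0.50 | 0 | 0.80 | 0.363 | 0.603 | 40% |

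For a fixed raw difference, the calculated number of records would be 71%, 53% or 36% of the number required. If selection is unrelated to completeness, every error is zero.

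**4. What an SD error does to power, in either direction.** Assumptions, since the plan states none: two-sided alpha 0.05, planned power 80%, difference 0.3, true SD 1, clustering ignored. The correct number is 2 × (1.96 + 0.84)² / 0.3², or 175 per arm.

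| SD used in planning | n per arm | True power |
|---|---|---|
| 0.90 | 142 | 72% |
| 0.80 | 112 | 61% |
| 0.70 | 86 | 50% |
| 1.10 | 212 | 87% |
| 1.20 | 252 | 92% |

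An SD that is too low costs power; one that is too high is conservative.

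**5. Chance error alone.** With 100 random folders, the 95% limits for the SD are √(99/χ²), about 0.88 to 1.16 times the estimate. A random draw removes selection error, not this uncertainty.

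**The case against.** A reader might infer that the feasibility figures will be too favourable. The documents do not support that. Nothing in the plan says that folders easy to reach are fuller, and the table in step 3 rests wholly on an assumed loss of the thinnest ones. An error in the safe direction is equally compatible with the text.

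A reader might also extend the criticism to staff. That does not hold. Despite the word convenience, section 3.1.2 will "recruit all eligible staff members who wish to take part in the study", section 3.1.4 approaches those who qualify one by one, and section 3.2.2.3 recruits trial staff in the same way. Uptake over eligible staff can be computed. The condition that "the hospital authorities must be ready and willing to participate in this feasibility study" does rule out estimating hospital willingness from this site, but the plan does not say that willingness is meant at hospital level, and no formula uses it.

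Other points against the concern stand in part:

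- Data availability is only listed as something the parameters could include. No go/no-go rule depends on it.
- The provisional 8 hospitals and 800 records do not depend on the feasibility SD.
- Section 3.2.2 says the trial population is the same as in the feasibility study, so it would go too far to call the feasibility folders a different population.
- The missing between-hospital ICC matters more for size. With 100 records per hospital the design effect 1 + 99 × ICC runs from 1.99 to 20.8 for assumed ICCs of 0.01 to 0.20. That is a separate gap, and closing it would not cure this one.

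None of this removes the conflict between the stated reason in section 3.1.2 and the stated use in section 3.2.2.2.

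**Conclusion.** The concern holds for the folders. The reason given for convenience sampling is inconsistent with using the feasibility mean and SD in the trial's sample size calculation. The set as described gives no availability rate, and its mean and SD may not transfer.

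The direction and size of any error are unknown. An SD understated by about 16% to 40% is what follows if the thinnest 10% to 50% of folders are missed and scores are normal; it is not an estimate of what will happen. The change is worth making because it is cheap and removes the need to guess at selection within the hospital.

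**What to change.** 1. In section 3.1.2, delete the generalisability reason as it applies to folders, and state how the 100 divide between pre-training and post-training records.
2. Draw the pre-training (baseline) folders at random within ward from a list of discharges, under the trial's criteria including the stay of at least five days. This assumes that such a list exists; the plan does not mention one.
3. Do not replace missing or unusable folders. Report them over the number sought as the availability result.
4. Compute the mean and SD for the sample size calculation from this random sample.
5. For post-training folders, which need patient or guardian consent, take consecutive eligible discharges and report non-consent separately from missing folders.

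The cost is a rewritten paragraph, a little more time to retrieve named folders, and slightly fewer than 100 usable ones. No extra hospital or larger draw is needed.
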